## Abstract

**Background:**

Peripheral arterial disease (PAD) and local infections increase the risk of non-healing diabetic foot ulcers (DFU) and limb amputations but are treatable by percutaneous transluminal angioplasty (PTA), local wound care and antibiotic therapy. The exact time to treat chronic leg artery stenosis (LAS) and the role of microbiome composition in DFU remain unclear. This study aims to assess whether an early PTA within 48 h after diagnosing a LAS offers advantages over standard care.

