This RCT will assess whether PTA within 48 h improves wound healing and reduces complications in participants with chronic ischemic DFUs over a 12-month period compared to standard care. The primary endpoint is the effect of early PTA on wound healing. Secondary endpoints include the combined occurrence of major adverse limb events (MALE), which serve as limb-specific outcomes, and major adverse cardiac events (MACE), which are considered safety-related secondary outcomes. Additional secondary endpoints include time to complete wound healing, major (above-ankle) amputation rate, and the need for new revascularization. Explanatory objectives are changes in wound microbiome composition and local microcirculation. The findings will inform the timing of PTA in managing DFS and help tailor more personalised and effective interventions for T2D persons. The study will also explore whether the baseline wound microbiome can predict healing outcomes.

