## Methods/design

### Study design and randomisation protocol

The PTA-DFS Study is a prospective, monocentric, RCT including participants with T2D and ischemic DFU. Ethics approval was obtained from the local ethics committee (Heinrich Heine University, Düsseldorf, Germany) in accordance with the Declaration of Helsinki (#2022–2291). The PTA-DFS study is registered at www.clinicaltrials.gov (NCT06124586; Registration Date: 2023–08-2).

Participants will be randomly assigned in a 1:1 ratio to either the early PTA group (‘immediate PTA‘ within 48 h after leg artery stenosis (LAS) diagnosis or the elective PTA group (standard of care with PTA within 6 weeks) at the academic hospital of the Heinrich Heine University Düsseldorf, Germany, with inclusion of 200 participants within 5 years. All study participants included in the study will provide informed consent. Although the study is unblinded for both participants and physicians due to practical feasibility, blinding will be applied during the data analysis phase, with separate analysis of primary and secondary endpoints by interventionists (physicians or clinicians) and data analysts to minimise bias. After the data is unblinded, all results will be reviewed collectively. This approach aims to ensure more accurate and unbiased analysis of the primary and secondary endpoints.

Randomisation is performed using a computer-generated sequence with block randomisation to ensure unbiased allocation. The block size will be specified in advance, using blocks of 4 or 6, to maintain balance across groups throughout the study. Both groups receive standard care, with the only difference being the timing of the PTA procedure. The study is structured to ensure that, apart from the timing of PTA, all other aspects of care are consistent across both groups. All subsequent laboratory analyses will be performed in a blinded manner, without knowledge of randomisation. Aside from the timing of PTA, baseline and follow-up examinations will be conducted uniformly across both groups. To optimise recruitment efficiency, training sessions will be held with the interventional angiology staff and the diabetic foot care team, ensuring participants and staff are fully informed about study-related procedures and analyses during their state-of-the-art clinical care.

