As illustrated in the study flow (Fig. 1), data will be collected at baseline recruitment (V0), during the index hospitalisation (V1; PTA and 24 h thereafter), and at follow-up visits at 1 (V2), 2 (V3), 3 (V4), 6 (V5), and 12 months (V6) post-PTA. If complications in wound healing occur in the elective group, crossover to the ‘immediate‘ PTA group will be implemented. Each patient will receive guideline-directed therapy for DFU, monitored and documented by specialised staff during clinical follow-ups and all study visits. Table 1 outlines the key analyses and corresponding time points throughout the study.

**Table 1 Tab1:** Study protocol. Table showing most relevant analyses and respective time points during the study period

Action								
**Visit (V)**	**Baseline**	**PTA**	**Follow-ups**					
	**V0**		**V1**	**V2**	**V3**	**V4**	**V5**	**V 6**
Time Point	0	0	0	1	2	3	6	12
Enrolment								
Eligibility Screen	X							
Informed Consent	X							
Randomisation	X							
Pseudonymisation	X							
Intervention		X						
Assessments								
Doppler/Duplex ultrasound	X		X	X	X	X	X	X
Segmental pulse oscillography	X		X	X	X	X	X	X
DSNP Screening (NDS, NSS)	X							
AI-based wound area documentation	X		X	X	X	X	X	X
Wound tissue oxygenation (NIRS)	X		X	X	X	X	X	X
AI-based retinal imaging	X							
TTE	X							
Fasting blood Sampling & Biobanking	X		X	X	X	X	X	X
Wound Swabbing & Biobanking	X		X	X	X	X	X	X
Wound Sampling & Biobanking	X		X	X	X	X	X	X
Urine Measurement	X							
Questionnaires	X		X	X	X	X	X	X
Outcome Assessment								
Primary Endpoint (wound healing)			X	X	X	X	X	X
Secondary Endpoint (MACE/MALE)			X	X	X	X	X	X

*DSPN* Distal symmetric polyneuropathy, *NDS* Neuropathy Disability Score, *NSS* Neuropathy Symptom Score, *AI* Artificial intelligence, *NIRS* Near-Infrared Spectroscopy, *TTE* Transthoracic Echocardiogram, *PTA* Percutaneous transluminal angioplasty, *MALE* Major adverse limb events, *MACE* Major adverse cardiac events

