**Fig. 1 Fig1:**
[figure not shown]
Timeline. The figure shows follow-up visits at respective time points during the study period. The specified times of the respective follow-up examinations refer to the time after the PTA. PTA = Percutaneous transluminal angioplasty, PAD = Peripheral arterial disease, T2D = Type 2 diabetes, DFU = Diabetic foot ulcer, RCT = Randomised controlled trial

The primary endpoint of the PTA-DFS Study is to assess the effect of early PTA on wound healing in T2D participants and chronic ischemic DFU. Wound healing is measured by the reduction of 3D wound area, assessed using clinical grading and 3D-camera analysis with AI-based evaluation of wound length, width, and depth. The secondary endpoint is the combined incidence of MALE and MACE post-angioplasty between early and elective PTA treatment, time to complete wound healing, major amputation rate and the need for new revascularization. Explanatory variables for the primary endpoint are differences in quantitative shifts in bacterial taxa with different oxygen requirements (aerobes, anaerobes) (Fig. 2). These shifts post-PTA will be analysed using appropriate statistical methods, such as Generalised Linear Mixed Models (GLMMs), accounting for treatment group (early PTA vs. elective PTA), bacterial taxa, and time, with random effects to adjust for individual variability. Another explanatory variable for wound healing is the change in oxygen saturation in the wound environment, measured by multispectral near-infrared spectroscopy (NIRS). These outcomes will be analysed using Cox proportional hazard models using time-to-event outcome for MALE/MACE events, adjusting for baseline covariates to evaluate the effectiveness of early PTA compared to standard treatment.

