### Imaging and ulcer evaluation

Wound documentation includes a 3D camera with an AI-based wound analysis system (Curevision®, Munich, Germany) to objectively assess wound healing progress. The system analyses wound dimensions (length, width, area and depth), wound tissue (granulation, fibrin, and necrosis) in the wound bed, and provides consistent, non-operator-dependent data [35]. Wound documentation will be conducted at each follow-up visit until wound closure is confirmed. Tissue involvement, including possible osteomyelitis, is investigated by X-ray, computed tomography or magnetic resonance imaging if clinically indicated.

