One explanatory variable evaluates the effect of early PTA on wound microbiome dynamics. This objective aims to measure the beta-diversity changes of the wound microbiome, assessed via whole-genome sequencing and analysed using Bray–Curtis distances. In detail, taxonomic profiles from whole-genome sequencing of the wound microbiome will be generated using bioinformatics scripts. The sequencing data, produced via the Oxford Nanopore platform [36] will be analysed with Kraken2 [37] and minimap2 [38] based on a custom database including protozoan, fungal, and viral sequences. Visualisations for comparing metagenomic composition across taxonomic levels will be generated with custom scripts. Principal coordinate analysis based on Bray–Curtis distances will assess sample clustering, with the entire workflow provided as a reproducible Snakemake pipeline [39]. Effect sizes are based on expected changes in Bray–Curtis distances for beta-diversity. Nominal variables will be compared using the Chi-Square Test and Fisher's Exact Test where appropriate. Relationships between variables (e. g., changes in wound microbiome or local microcirculation and wound healing or complications) will be assessed using partial Pearson or Spearman correlation coefficients, with adjustments for confounders and multiple testing via the Bonferroni or Benjamini–Hochberg method. The standardised mean difference (Cohen's d) will be used for power analyses due to the lack of preliminary data on changes of ulcer area and combined incidence of MALE/MACE after early PTA. Changes in beta-diversity of the wound microbiome, will be analysed using Generalised Linear Mixed models with fixed effects including treatment group, bacterial taxa, time, and random effects to account for patient variability. Interaction terms will assess differential effects between treatment groups. The secondary endpoint includes combined MALE and MACE incidence post-angioplasty. Oxygen saturation in wound environment is measured as another explanatory outcome potentially linked to wound healing. Additional outcomes will include an evaluation of risk factors such as comorbidities (severity of anaemia and stages of chronic kidney disease), severity of insulin resistance, DSPN, the duration of hospital stay and interactions with medications, including antibiotics and antithrombotic therapies. Risk endpoints include the incidence of MALE, progression of diabetic complications (e.g., neuropathy), and hospital stay duration. These will be analysed using survival analysis methods and logistic regression to evaluate risk/benefit ratios. Multiplicity will be addressed as follows: The primary outcome will be analysed at a two-sided significance level of 0.05 without adjustment. For the prespecified family of confirmatory secondary outcomes, the family-wise error rate will be controlled at 0.05 using the Holm–Bonferroni procedure. For these outcomes, raw and adjusted p-values as well as corresponding adjusted 95% confidence intervals will be reported. Exploratory outcomes will not be adjusted for multiplicity and will be clearly identified as exploratory. Safety outcomes will be reported descriptively. The interaction effects of antibiotics, PTA timing, and concomitant antithrombotic treatments on both primary and secondary endpoints will be assessed using logistic regression models and subgroup analyses. Time-to-event clinical endpoints will be analysed with Kaplan–Meier survival curves, while covariate adjustments will be incorporated using Cox proportional hazards models. Correlation analyses (partial Pearson or Spearman coefficients) will account for confounders and include multiple comparison corrections via Bonferroni or Benjamini–Hochberg adjustments. Categorical variables will be compared using Chi-Square or Fisher's Exact Tests, while continuous variables will be analysed with Wilcoxon rank-sum tests or Student's t-tests, as appropriate. Two-tailed p-values below 0.05 will be considered statistically significant. Missing data will be summarised by variable, time point, and treatment arm, and patterns of missingness will be described graphically and statistically. The primary analysis will employ multiple imputation by chained equations (MICE; m = 20 imputations) under the assumption of missing at random (MAR). The imputation model will be specified to be congenial with the planned analysis and will include treatment arm, relevant baseline covariates (e. g., age, sex, ulcer duration, ulcer size, Wagner grade, HbA1c, infection status), and outcome variables. Continuous variables will be imputed using predictive mean matching, binary variables will be analysed via logistic regression, and ordinal variables will be analysed using proportional-odds models. Estimates will be combined using Rubin’s rules. Sensitivity analyses will include (i) complete-case analysis, (ii) best–worst and worst–best case scenarios, and (iii) a delta-adjusted pattern-mixture model to assess departures from MAR and exploring missing not at random (MNAR). All statistical analyses will be performed using the R Version 4.4 and SPSS for Windows 23.0 (SPSS Inc., Chicago, IL, USA). Figures are created with GraphPad Prism, Version 7.01 (GraphPad Software, Inc., La Jolla, CA, USA) or R, and Graphical abstracts using BioRender.com.

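### Visits that detect wound closure are counted from PTA, whose timing is randomised, and no time origin is fixed for time to complete healing, so the planned Kaplan–Meier and Cox analysis can be biased in either direction

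*Protocol article*

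**What the plan says.** All references are to the Protocol article.

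- **Endpoint.** Background: "Additional secondary endpoints include time to complete wound healing, major (above-ankle) amputation rate, and the need for new revascularization".
- **How closure is observed.** Imaging and ulcer evaluation: "Wound documentation will be conducted at each follow-up visit until wound closure is confirmed".
- **When the visits are.** Study design and randomisation protocol: "at follow-up visits at 1 (V2), 2 (V3), 3 (V4), 6 (V5), and 12 months (V6) post-PTA". The Fig. 1 legend confirms the anchor: "The specified times of the respective follow-up examinations refer to the time after the PTA".
- **The randomised contrast.** The Abstract asks "whether an early PTA within 48 h after diagnosing a LAS offers advantages over standard care". Under Study design and randomisation protocol, the comparator is "standard of care with PTA within 6 weeks".
- **The analysis.** Statistical methods and power calculation: "Time-to-event clinical endpoints will be analysed with Kaplan–Meier survival curves", with Cox models to adjust for covariates. No method for interval-censored data is named.
- **Time origin.** The power statement counts time to event from baseline, and the Abstract counts 12 months from angioplasty. Both remarks concern MALE/MACE. None is made for healing.

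**The concern.** A wound seen open at one visit and closed at the next closed at some unknown time in between. Between the 6- and 12-month visits that gap is 6 months. Kaplan–Meier and Cox need an event date. If the date of the detecting visit is used, every closure is recorded late. This does little harm to a comparison when both arms are inspected at the same times. Here allocation sets the PTA date and the PTA date sets the visits, so the delay in detection differs by arm.

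The choice of clock then decides the direction of the error. A clock from randomisation keeps the visits out of step. A clock from PTA aligns them but removes the elective wait, which is the difference between the randomised strategies. At stake is the hazard ratio for a patient-relevant secondary outcome. A multiplicity procedure cannot correct a biased estimate.

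**Working it through.** **1. The plan's own figure.** The only computed figure is the sample size. For d = 0.4, two-sided 5% and 80% power, n = 2(1.960 + 0.842)²/0.4² = 98.1, so 99 per arm (99.1 by the t-test). Power at 100 per arm is 80.7% (80.4% by the t-test). The stated 100 per arm reproduces and is not affected by this point.

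**2. Inputs.** From the article: visits at PTA + 24 h, 1, 2, 3, 6 and 12 months; early PTA within 48 h; elective PTA within 6 weeks; 100 per arm; two-sided 5%. Assumed, because the article gives none: the share healed by 12 months, the shape of the healing curve, the distribution of the elective wait, and randomisation close to diagnosis. Early PTA is set at 2 days (2/30.4 = 0.07 months). The elective wait is uniform from there to 6 weeks (42/30.4 = 1.38 months, mean 0.72), or fixed.

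**3. The mechanism in one example.** Take constant-hazard healing with 60% healed by 12 months, identical in both arms from randomisation: λ = −ln(0.4)/12 = 0.0764 per month.

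- Early arm, last visit at 12.07 months: closed by then = 1 − exp(−0.0764 × 12.07) = 60%, all recorded.
- Elective arm, last visit on average at 12.72 months: closed by then = 1 − exp(−0.0764 × 12.72) = 62%.
- Elective arm, 6-month visit on average at 6.72 months: closed by then = 1 − exp(−0.0764 × 6.72) = 40%. Almost no elective participant has had the 12-month visit by 12.1 months, so only about 41% are recorded as healed then (simulated value).

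Healing is equal, yet the record at 12.1 months shows 60% against 41%. The remaining elective closures (62 − 41 = 21 percentage points) are recorded after the last early-arm visit, when nobody in the early arm is at risk, so they add nothing to the Cox or log-rank comparison.

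**4. Simulation with no true effect.** Clock at randomisation, closure dated at the detecting visit unless stated, 100 per arm:

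| Healing or dating assumption | Hazard ratio (>1 favours early PTA) | Rejection at 5% |
|---|---|---|
| Constant hazard, 40–80% healed by 12 months | 1.32–1.74 | 33–64% |
| 60% healed, Weibull shape 0.7 | 1.36 | 27% |
| 60% healed, Weibull shape 1.5 | 2.08 | 86% |
| Some never heal; healers' mean about 2 months | 1.02–1.13 | 3–10% |
| Some never heal; healers' mean 4 months | 1.15–1.28 | 11–26% |
| Healing spread over the year, half of closures exactly dated | 1.14–1.34 | 13–30% |
| Same, 80% exactly dated | 1.10–1.13 | 6–9% |
| 60% healed, closure dated every 2 weeks in both arms | 0.99–1.01 | 5–6% |

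Random visit deviations (SD 0.1 month) enlarge the effect, up to a hazard ratio of 2.17 and 88% rejection. Censoring at 7.5 months turns it slightly the other way (0.90–0.98, 5–9%), so the 6-to-12-month gap is the main driver.

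**5. Clock at PTA.** If healing is equal counted from PTA, the hazard ratio is 0.99–1.01 with 5–6% rejection: no visit artefact. If healing is equal counted from randomisation, the elective times are shortened by the wait, and the hazard ratio is about 0.77–0.95 against early PTA.

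**6. Remedies, clock at randomisation, 60% healed.** A Weibull interval-censored model gives 0.98–1.01 with 3–4% rejection. A common visit calendar from randomisation gives 0.99–1.00 with 5–6%.

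**The case against.** **Closure may not be seen only at study visits.** A reader might infer that it is. The article does not say so: under Study design and randomisation protocol, ulcer therapy is also documented at clinical follow-ups, and no sentence makes the detecting visit the event date. This stands. It reduces the bias, and frequent dating in both arms removes it. But that remark concerns therapy, wound documentation is tied to follow-up visits, and dating half of the closures is not enough.

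**The rule may sit in the statistical analysis plan, which is not shown.** This is fair for the dating rule, and the Kaplan–Meier and Cox sentence suits amputation, revascularisation and death. But the article itself fixes both the method for time-to-event endpoints and a visit schedule that does not fit it for healing.

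**It is tempting to say that the visit schedule alone must create a false difference.** That needs a clock at randomisation, which the article does not fix for healing. With a clock at PTA the visits align. The error there comes from the dropped wait, and interval censoring would not cure it.

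**The large figures rest on one kind of healing curve.** This also stands: early healing with a never-healing fraction brings the error close to nominal.

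**A reader might take time to healing as part of the confirmatory family.** The article does not list that family, so this is an inference.

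**The Weibull remedy was tested on Weibull data.** True, and a reason to prefer a flexible baseline hazard. Crossover was not simulated either.

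**Conclusion.** The concern holds in conditional form. The visits that detect closure are tied to an event whose timing is randomised, the origin for time to healing is open, and the stated methods assume dated events.

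With a clock at randomisation and visit-dated closure, the bias runs towards early PTA. It ranges from a hazard ratio of about 1.05 with near-nominal error to about 1.3–2.1 with 27–86% false positives. Where the trial falls depends on how much healing occurs between 6 and 12 months and on how many closures are dated outside visits, neither of which the article gives. With a clock at PTA, the hazard ratio is about 0.77–0.95 against early PTA if healing is equal from randomisation.

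The documents do not support a claim that bias is certain or that it has one known size. The point is worth settling before analysis because the possible error is large and the correction is small.

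**What to change.** State randomisation as the time origin for time to complete healing, and analyse it as interval-censored. The lower limit is the last visit with an open wound and the upper limit is the first visit with confirmed closure. Where a closure date is documented, use that date. Fit an interval-censored proportional hazards model with treatment arm and the planned covariates, preferably with a flexible baseline hazard, and show a Turnbull curve in place of Kaplan–Meier. Keep Kaplan–Meier and Cox for exactly dated events such as amputation, revascularisation and death.

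The cost is a sentence or two in the analysis plan, a standard R package, slightly more analysis work and less familiar output. No new data or visits are needed. Wound assessments on a common calendar from randomisation would also remove the artefact, but would change the visit schedule.

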### Statistical methods and power calculation

The primary endpoint focuses on the difference in changes of wound area (delta wound area at first - last visit) in T2D participants after early PTA compared to individuals with standard PTA. For the primary—change in wound area after early PTA—and secondary endpoint—combined incidence of MALE and MACE—a power calculation was performed. Assuming a medium effect size (Cohen's d = 0.4), corresponding to 0.4 standard deviations of the difference in delta wound area and difference in time-to-event from baseline to last visit between groups, a sample size of n = 100 per group (total n = 200) is required to achieve 80% power at alpha = 0.05.

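### One 12-month Cox hazard ratio is likely to dilute the effect of the six-week wait, or to leave the wait out if time runs from PTA

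*Protocol article*

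**What the plan says.** **Contrast.** Under Study design and randomisation protocol, the early arm has PTA "within 48 h after leg artery stenosis (LAS) diagnosis" and the elective arm receives "standard of care with PTA within 6 weeks". Both arms get standard care, "with the only difference being the timing of the PTA procedure". Elective participants whose wound healing is complicated may cross over to immediate PTA.

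**Analysis.** The text below Figure 1 says: "These outcomes will be analysed using Cox proportional hazard models using time-to-event outcome for MALE/MACE events", with adjustment for baseline covariates. The section Statistical methods and power calculation says: "Time-to-event clinical endpoints will be analysed with Kaplan–Meier survival curves", and that "covariate adjustments will be incorporated using Cox proportional hazards models". No contrast between the Kaplan–Meier curves is named.

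**Time zero.** The Abstract, the text and legend at Figure 1, the statistical section and the Conclusion all place the MALE/MACE composite after angioplasty, and visits are timed from PTA in each arm. The power paragraph instead speaks of the "difference in time-to-event from baseline to last visit between groups". No sentence defines time zero for the Cox model.

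**The concern.** A Cox model with one treatment term summarises the year by one ratio, which is easy to interpret only if that ratio is roughly constant. Here the randomised difference in treatment lasts from about day 2 to day 42 at most. After that every participant has, by plan, had PTA. The hazard ratio can stay constant only if the effect of the delay carries over at the same strength, or if there is no effect at all.

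The trial asks what acting within 48 h gains. From randomisation, a single ratio mixes the wait with a much longer period of equal treatment, so its value depends on the length of follow-up. From PTA, it compares participants only after each has been treated. Elective participants must then reach PTA event-free to contribute, and the events that early PTA is meant to prevent are not counted.

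**Working it through.** **The plan's own figure.** For d = 0.4, 80% power and two-sided alpha of 0.05, n per group = 2 × (1.960 + 0.842)² / 0.4² = 2 × 7.85 / 0.16 = 98.1, so 99 (99.1 by t-test). The stated 100 per group reproduces. It is a two-means calculation with no hazard ratio or event rate, so it says nothing about the Cox model.

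**Inputs.** From the protocol: 100 per arm, early PTA by day 2, elective PTA by day 42, 12 months. Assumed, because the protocol gives none: 40% 12-month risk at the post-PTA hazard, a hazard three times higher before PTA, elective PTA uniform on days 14–42 (mean 28), time from randomisation, no crossover and no carry-over.

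**Clock from randomisation.**
1. Post-PTA hazard: λ = −ln(0.60) / 365 = 0.00140 per day.
2. Cumulative hazard to day 42. Early: 2 × 3λ + 40λ = 46λ = 0.064, about 6 events per 100. Elective at the mean wait: 28 × 3λ + 14λ = 98λ = 0.137, about 13 per 100.
3. Hazard ratio in days 0–42: 46/98 = 0.47 (simulated: 0.46). After day 42: 1.00.
4. Cumulative hazard to day 365. Early: 46λ + 323λ = 369λ, 40.3 events per 100. Elective: 98λ + 323λ = 421λ, 44.5 per 100.
5. Share of events before day 42: (6.2 + 12.8) / (40.3 + 44.5) = 0.22. The Cox log hazard ratio is roughly the event-weighted mean: 0.22 × ln 0.47 + 0.78 × ln 1 = −0.17, so the ratio is about 0.85. Simulation also gives 0.85.

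| Assumed hazard before PTA | HR days 0–42 | HR after | 12-month Cox HR |
|---|---|---|---|
| 3× (MALE/MACE) | 0.46 | 1.00 | 0.85 |
| 5× (MALE/MACE) | 0.33 | 1.00 | 0.74 |
| 0.05× (healing, 75% by 12 months) | 2.7 | 1.0 | 1.13 |

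In the healing case the restricted mean difference is about 18 days.

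**A second parameterisation.** Flat elective hazard, 30% 12-month risk, elective PTA at week 6, hazard ratio 0.5 during the wait and 1.0 afterwards. The wait is 6/52 = 11.5% of the year and holds about 10% of events, so exp(0.10 × ln 0.5) = 0.93. Varying the 12-month risk (20–40%), the wait hazard ratio (0.3–0.7), the early hazard (flat or threefold) and the PTA timing (week 6, or spread over weeks 0–6) gives 0.77–0.98.

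**With carry-over.** In the 3× case, let the elective hazard stay 1.3 times higher after PTA. Days 0–42: 46 / (84 + 14 × 1.3) = 46/102.2 = 0.45. Afterwards: 1/1.3 = 0.77. Simulated Cox: 0.69. The ratio still changes, but less.

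**Clock from PTA.** In the 3× case without carry-over, both arms have hazard λ after PTA, so the ratio is 1.00. Events before PTA are excluded: about 1 − exp(−84λ) = 11% of the elective arm at the mean wait, against 1 − exp(−6λ) = 0.8% of the early arm. The whole benefit lies in what is left out.

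**Power, Cox against RMST (simulated).**

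| Elective hazard before, then after PTA | Cox | RMST |
|---|---|---|
| 3×, then 1× | 12% | 19% |
| 5×, then 1× | 29% | 47% |
| 3×, then 1.5× | 67% | 68% |
| 2×, then 1.5× | 54% | 49% |
| Proportional, HR 0.6, 40% control events | 54.5% | 47.6% |

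The direction of any power difference depends on carry-over.

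**The case against.** The strongest objection is that equal treatment does not mean equal hazards. The Discussion argues that delay worsens hypoxia, infection and tissue damage, and tissue lost while waiting can raise limb risk for months. If a ratio of 0.5 persists unchanged, the Cox ratio is 0.50 throughout; with no effect it is 1 throughout. This stands. A reader might infer that the hazard ratio cannot be constant by design, or must return to 1 after week 6, and the protocol does not support that. The later ratio of 1.00 in the main example is an input, not a result.

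Second, most of the article times events from PTA, and on that clock nothing is averaged. This also stands, but it replaces dilution with omission and does not rescue the estimate.

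Third, the protocol nowhere says that one hazard ratio carries the conclusion. Kaplan–Meier curves are planned, and logistic regression is named for risk endpoints including MALE incidence. Checks of proportional hazards commonly belong in an analysis plan that is not shown, so their absence is no fault. What remains is that the article names a proportional-hazards model for a contrast of at most six weeks and leaves time zero contradictory.

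Last, a reader might infer that RMST would give more power. The table above shows that the advantage vanishes or reverses with carry-over.

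**Conclusion.** The point holds as a modest, inexpensive improvement to secondary endpoints. A constant hazard ratio is unlikely, though not impossible, because the randomised contrast covers at most about six weeks of twelve months.

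- **From randomisation, with little carry-over:** one ratio dilutes the effect of the wait, for example from about 0.46 to about 0.85. The size rests entirely on assumed hazards. Crossover is not modelled and would shorten the wait for some participants.
- **From PTA:** the wait and its events are omitted. This follows from the definition of the clock and needs no assumed hazards.

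The conflict over time zero is in the text and needs correcting whatever the carry-over.

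**What to change.** 1. **Time zero.** Reconcile the post-angioplasty wording in the Abstract, at Figure 1, in the statistical section and in the Conclusion with the power paragraph, using randomisation as the origin in both arms. Randomisation is at V0, before PTA, so a 12-month post-PTA visit already reaches 365 days from randomisation. Events between randomisation and PTA need dates.
2. **Effect measure.** Keep the log-rank/Cox test. Beside it, prespecify the covariate-adjusted difference in restricted mean event-free time (MALE/MACE) and unhealed time (healing) to 365 days from randomisation.
3. **Period-specific hazard ratios.** Those for days 0–42 and after day 42 should be descriptive only. With about 6 and 13 early events, the standard error of the log ratio is about √(1/6 + 1/13) = 0.49, so 0.46 would have a 95% interval of roughly 0.17 to 1.2. The later ratio compares only those still event-free.

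The cost is analysis wording and a little programming, with no added participants or visits. RMST is somewhat less precise if hazards are proportional (about 7 points of power in the case above), which is why the existing test stays.
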